#### 2. Date of assessment: dd/mm/yyyy

**3. Following their assessment, has the child received an ADHD diagnosis from the service they were initially referred to?**

Yes (go to question 4)

No (go to question 6)

**4. Date of diagnosis: dd/mm/yyyy**

**5. Has the child received another diagnosis?**

Autism spectrum disorder (ASD)

Conduct disorder

Oppositional defiant disorder

Other

No diagnosis

**6. Has the child received treatment?**

No treatment

Yes, medication (Go to Q7)

Yes, psychological treatment for the child

Yes, parenting support

**7. Name of medication and dose [free text 100 characters]**

## APPENDIX 2

### Trial expectations questionnaire

In this questionnaire, we would like to find out about your general expectations and experience of parent training.

1. Have you ever taken part in a research study before (online or face to face)?

Yes (1)

No (0)

2. Have you ever taken part in a research study specifically on parenting before (online or face to face)?

Yes (1)

No (0)

3. Please rate your agreement with the following statements about parent training.

Overall, I think parent training is/would be:

Helpful to me as a parent

Strongly disagree (1)

Somewhat disagree (2)

Not sure (3)

Somewhat agree (4)

Strongly agree (5)

Helpful to my child

Strongly disagree (1)

Somewhat disagree (2)

Not sure (3)

Somewhat agree (4)

Strongly agree (5)

A good use of my time

Strongly disagree (1)

Somewhat disagree (2)

Not sure (3)

Somewhat agree (4)

Strongly agree (5)

Not enough reward for the time it takes to get involved

Strongly disagree (1)

Somewhat disagree (2)

Not sure (3)

Somewhat agree (4)

Strongly agree (5)

A waste of time

Strongly disagree (1)

Somewhat disagree (2)

Not sure (3)

Somewhat agree (4)

Strongly agree (5)

4. We would like to find out about your *expectations* of using the STEPS parenting app. Based on what you have been told about it, please rate your agreement with the following statements about STEPS.

STEPS would help me feel better about my parenting

Strongly disagree (1)

Somewhat disagree (2)

Not sure (3)

Somewhat agree (4)

Strongly agree (5)

STEPS would help me manage my child better

Strongly disagree (1)

Somewhat disagree (2)

Not sure (3)

Somewhat agree (4)

Strongly agree (5)

STEPS would improve my knowledge about parenting

Strongly disagree (1)

Somewhat disagree (2)

Not sure (3)

Somewhat agree (4)

Strongly agree (5)

STEPS would improve my mental health

Strongly disagree (1)

Somewhat disagree (2)

Not sure (3)

Somewhat agree (4)

Strongly agree (5)

STEPS would improve our family life

Strongly disagree (1)

Somewhat disagree (2)

Not sure (3)

Somewhat agree (4)

Strongly agree (5)

STEPS would improve my child's behaviour

Strongly disagree (1)

Somewhat disagree (2)

Not sure (3)

Somewhat agree (4)

Strongly agree (5)

STEPS would improve my relationship with my child

Strongly disagree (1)

Somewhat disagree (2)

Not sure (3)

Somewhat agree (4)

Strongly agree (5)

STEPS would improve my child's mental health

Strongly disagree (1)

Somewhat disagree (2)

Not sure (3)

Somewhat agree (4)

Strongly agree (5)

STEPS would help my child feel happier

Strongly disagree (1)

Somewhat disagree (2)

Not sure (3)

Somewhat agree (4)

Strongly agree (5)

STEPS would help my child do better at school

Strongly disagree (1)

Somewhat disagree (2)

Not sure (3)

Somewhat agree (4)

Strongly agree (5)

5. Please use the text box below to tell us more about your hopes and/or worries about using the STEPS parenting app.

[free text 500 characters]

6. If you could choose, would you prefer face to face parent training (where you meet in person with a therapist who explains things to you) or online parent training delivered via an app (such as STEPS)?

Face to face (1)

Online (2)

No preference, as long as I get help and support (3)

## APPENDIX 3

### Medical and psychological events and difficulties questionnaire

We want to keep track of whether there are any potential concerns about taking part in OPTIMA. These questions will ask about any **physical** and **mental health difficulties your child** and **you** may have experienced in the last **3 months**. We will also ask about any difficulties **your child** and **you** may have had with daily activities.

This section will ask about any **physical health** or **medical** problems. We will first ask about **your child** and then ask about **you**.

1. Has **your child** had any **physical health** or **medical** problems in the last 3 months?

**NO: go to Q2**

**YES:**

- Please say a bit more about the problem [500 characters]
- When did this problem start? Please provide approximate date.
- When did this problem end? Please provide approximate day or select 'ongoing' if not resolved.
- Did this problem result in hospitalisation? **Yes/No**. If yes, please describe [500 characters].

2. Have **you** had any **physical health** or **medical** problems in the last 3 months?

**NO: go to Q3**

**YES**

- Please say a bit more about the problem [500 characters]
- When did this problem start? Please provide approximate date.
- When did this problem end? Please provide approximate day or select 'ongoing' if not resolved.
- Did this problem result in hospitalisation? **Yes/No**. If yes, please describe [500 characters].

This section will ask about any **mental health** or **behavioural** problems. We will first ask about **your child** and then ask about **you**.

3. Has your child had any **mental health** or **behavioural** problems in the last 3 months?

**NO: go to Q4**

**YES**

- Please say a bit more about the problem [500 characters]
- When did this problem start? Please provide approximate date.
- When did this problem end? Please provide approximate day or select 'ongoing' if not resolved.
- Did this problem result in hospitalisation? **Yes/No**. If yes, please describe [500 characters].

4. Have you had any **mental health** problems in the last 3 months?

**NO: go to Q5**

**YES:**

- Please say a bit more about the problem [500 characters]
- When did this problem start? Please provide approximate date.
- When did this problem end? Please provide approximate day or select 'ongoing' if not resolved.
- Did this problem result in hospitalisation? **Yes/No**. If yes, please describe [500 characters].

This section will ask about any **difficulties in relationships with family members you live with or daily activities**. We will first ask about **your child** and then ask about **you**.

5. Has your child had any **difficulties in relationships with family members you live with or daily activities** at home, school, including online schooling or things that they normally do in the last 3 months?

**NO: go to Q4**

**YES**

- Please say a bit more about the problem [500 characters]
- When did this problem start? Please provide approximate date.
- When did this problem end? Please provide approximate day or select 'ongoing' if not resolved.

6. Have you had any **difficulties in relationships with family members you live with or daily activities** at home, work or other things that you normally do in the last 3 months?

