### **10.3.9 Adverse events**

*T1, T2, T3, T4, T5, safety outcome.*

This will be measured with the Medical and psychological events and difficulties questionnaire (MAPED), which has been developed for the study (see Appendix 3). Parents will be asked to report retrospectively any physical and/or mental health difficulties they or their child have experienced in the last three months. They will also be asked to report any difficulties they or their child have had with daily activities. These will be used to monitor safety and to provide descriptive information about adverse events experienced during the trial.

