## 21. Harms

### 21.1 *Specification, Timing and Recording of Safety Parameters*

Please see section 21.2 below for adverse event definitions and reporting parameters. The risk of participants experiencing any adverse events during this trial as a result of using STEPS is very low. Adverse events concerning parental or child physical and mental health will be monitored throughout the trial. Any physical or mental health difficulties spontaneously disclosed by a parent in their communication with researchers will be entered into the Red Pill database using the OPTIMA adverse events form created specifically for the study (see Appendix 4). Moreover, at each timepoint, participants will be asked to complete a formal questionnaire on adverse events (Medical and psychological events and difficulties questionnaire) that happened to them and their child. This information will be collected online using ePRO. The forms will be reviewed regularly, and all adverse events will be recorded on the OPTIMA adverse events form in the Red Pill database. All participants that experience a serious adverse event will be followed-up by the researchers, who have completed Level 2 safeguarding training, until the event is resolved. Where necessary, the participant's clinical service which accepted the referral will be informed about the event.

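### The adverse event questionnaire asks about any problems but gives each domain one set of dates (and, in questions 1 to 4, one hospitalisation answer), so a second problem's details can be missing or misattributed

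*Protocol*

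**What the plan says.** Section 10.3.9 has parents report "retrospectively any physical and/or mental health difficulties they or their child have experienced in the last three months", at T1 to T5. It gives the purpose as follows: "These will be used to monitor safety and to provide descriptive information about adverse events experienced during the trial".

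Appendix 3 prints the questionnaire. It has six domain questions: physical health, mental health or behaviour, and relationships or daily activities, each asked for the child and then for the parent. The stems are plural. Questions 1 to 4 ask about "problems in the last 3 months", and questions 5 and 6 ask about difficulties over the same period. A YES answer opens one set of items in the singular:

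- a description: "Please say a bit more about the problem [500 characters";
- a start: "When did this problem start? Please provide approximate date";
- an end: "Please provide approximate day or select 'ongoing' if not resolved";
- in questions 1 to 4 only: "Did this problem result in hospitalisation", with a second free-text box if the answer is yes.

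The form then moves to the next domain. It does not ask whether there was another problem of the same kind.

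Section 21.1 says that the completed forms are reviewed regularly and that "all adverse events will be recorded on the OPTIMA adverse events form in the Red Pill database". Difficulties that a parent mentions spontaneously to researchers go onto the same form. That form, in Appendix 4, has columns for description, start date, outcome, end date, relationship to the intervention, expectedness, seriousness and the person affected.

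**The concern.** The record in Appendix 4 is built around a single event with its own dates and seriousness. The questionnaire that mainly feeds it is built around a domain. When a parent has two problems to report in one domain, the single pair of dates and the single hospitalisation answer cannot serve both. Either the parent chooses one, or both are described and nobody can tell which problem the dates and the hospitalisation answer belong to.

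Hospitalisation matters most, because section 21.2.1 makes it a criterion for a serious adverse event, section 21.1 reserves researcher follow-up for participants with a serious event, and section 21.2.2 uses the completed questionnaires to look for suspected unexpected serious reactions. A hospitalisation answer attached to the wrong problem, or not given because the parent was thinking of another one, weakens that chain.

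Question 3 is where this is most likely. Section 8.1 requires every child to have screened positive for conduct problems (SDQ score of 4 or more) and for hyperactivity/inattention (8 or more). A parent can therefore truthfully answer YES at every wave because of the problem that led to referral. A new event such as self-harm, which section 21.3 lists within deterioration in child behaviour, would share that one set of fields.

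**Working it through.** **What each form holds, for two problems A and B in the same domain and window**

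| Item | Appendix 3 offers | Appendix 4 holds per event | Left for B if the fields describe A |
|---|---|---|---|
| Description | one 500-character box | one description | can be typed in the same box |
| Start date | one | one | no field |
| End date or ongoing | one | one, plus outcome | no field |
| Hospitalisation | one in questions 1 to 4, none in 5 and 6 | one seriousness category | no field of its own in questions 1 to 4 |

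The description of B can survive. Its dates and hospitalisation status have nowhere of their own, and a reviewer who transfers the answer can use only what was collected. This part follows from the printed forms and needs no assumption.

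**Could counts be affected, and by how much?** The protocol has no adverse event rate or count to reproduce, so the following rests on assumed inputs. Suppose that events in one domain are Poisson with mean m per person per three months in the reference arm, that the other arm has true rate ratio R, that a domain never yields more than one record per window, and that there is no other route of capture. That is the worst case. Then:

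- share of events captured in the reference arm = (1 − e^(−m)) / m;
- ratio seen between arms = (1 − e^(−mR)) / (1 − e^(−m)).

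For example, at m = 0.5: 1 − e^(−0.5) = 0.3935, and 0.3935 / 0.5 = 0.787, so 21.3% is lost. With R = 1.5: 1 − e^(−0.75) = 0.5276, and 0.5276 / 0.3935 = 1.34.

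| m (assumed) | Share captured | Share lost | True ratio 1.5 seen as | True ratio 2.0 seen as |
|---|---|---|---|---|
| 0.05 | 97.5% | 2.5% | 1.48 | 1.95 |
| 0.1 | 95.2% | 4.8% | 1.46 | 1.90 |
| 0.3 | 86.4% | 13.6% | 1.40 | 1.74 |
| 0.5 | 78.7% | 21.3% | 1.34 | 1.61 |
| 1.0 | 63.2% | 36.8% | 1.23 | 1.37 |

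With R = 1 the ratio stays at 1.00 for every m. If staff split multi-problem answers into separate rows, the loss of counts shrinks or disappears, and only the attribution of dates and hospitalisation remains in doubt. A summary of participants with at least one event in a domain would not change under the cap. The Poisson model does not represent the standing problem in question 3, where the first slot is taken by something that is not a new event.

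**The case against.** A reader might infer that each domain accepts only one problem, that later events are lost, and that event counts are therefore too low and pulled towards no difference. The documents do not support this, for four reasons.

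- **No limit is stated.** The stems are plural and the 500-character box is free text. Nothing tells the parent to name only one problem.
- **The questionnaire is not the final record.** Section 21.1 puts a staff review between it and the adverse events form, and nothing stops a reviewer entering two rows from one answer. Spontaneous reports to researchers are a second route.
- **Hospital use is also collected elsewhere.** The service use schedule in section 10.4.1 covers hospital services at T1 to T5, although the protocol does not say that it feeds adverse event reporting.
- **There is no stated analysis to dilute.** Section 10.3.9 describes safety monitoring and description. No event rate and no between-arm comparison of counts is given.

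The questionnaire is also completed at T1, so a standing problem can be recognised at baseline. That parents would leave self-harm out of the text box is a possibility, not something that the protocol shows.

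All of this stands against the stronger reading. It does not supply the second pair of dates or the second hospitalisation answer. The trial is remote and the app unguided, with follow-up mainly online, so spontaneous disclosure cannot be relied on to fill the gap.

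**Conclusion.** The point holds as a weakness in data capture. For a second problem in the same domain and window, Appendix 3 has no fields for dates and, in questions 1 to 4, none for hospitalisation, while Appendix 4 needs them for each event. They may be misattributed or missing, and some second events may go unreported. Question 3 is the likeliest place.

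Any undercount, or dilution of a difference between arms, is possible but not quantified. The tabulated losses of 2.5% to 37% need assumed rates, a strict cap and no splitting by staff. Dilution also needs unequal rates and a comparison of event counts. The point does not touch the primary analysis. It is a cheap improvement to a stated collection tool, not a demonstrated bias in the safety results.

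**What to change.** After each YES block in questions 1 to 6, ask whether there has been any other problem of this kind in the last three months. Repeat the block (description, start date, end date or ongoing and, for questions 1 to 4, hospitalisation) until the answer is no. Enter one row on the Appendix 4 form per block.

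The change is a repeat-block setting in the electronic questionnaire. Families with several problems would take slightly longer to complete it. Waves completed before the change would remain on the single-block form, so the report should say which form was in use when.

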**NO: go to Q7**

**YES**

- Please say a bit more about the problem [500 characters]
- When did this problem start? Please provide approximate date.
- When did this problem end? Please provide approximate day or select 'ongoing' if not resolved.

7. Have any of the difficulties you described given you concerns about taking part in OPTIMA?

**NO: go to Q8**

**YES: please describe [500 characters]**

8. Did anything good happen to you or your child because of taking part in OPTIMA? (Any specific good things that have happened or things that have changed in a positive way to do with or because of taking part).

**NO: end of form**

**YES: please describe [500 characters]**

## APPENDIX 4

### Adverse Events Form

### Adverse Events Form

This form was completed based on:

1. A report from a research assistant?
2. A completion of an online questionnaire?

| 1. Details of adverse event
(describe below what has been reported)

[free text up to 500 characters] | 2. Medical/physical health
1. Cardiovascular
2. Respiratory
3. Hepatic
4. Gastro-intestinal
5. Genito-urinary/renal
6. Endocrine
7. Haematological
8. Musculo-skeletal
9. Neoplasia
10. Neurological
11. Psychological
12. Immunological
13. Dermatological
14. Allergies
15. Eyes, ear, nose, throat | 3. Mental health/behaviour

0. No
1. Yes | 4. Relationships or daily activities difficulties

0. No
1. Yes | 5. Start date | 6. Outcome
1. Resolved
2. Resolved with treatment/intervention
3. Ongoing | 7. End date | 8. Relationship to intervention
1. Definitely related
2. Likely
3. Possibly
4. Unlikely
5. Not related | 9. Expected?
1. Expected
2. Unexpected | 10. Is this event serious?
0. No
1. Results in death
2. Is life-threatening
3. Requires hospitalisation or prolongation of existing hospitalisation
4. Persistent or significant disability or incapacity
5. Consists of a congenital anomaly or birth defect | 11. SUSAR?
0. No
1. Yes | 12. Who is involved?
1. Target child
2. Target parent | 13. Has the event led to the family no longer participating in the study?
0. No
1. Yes |
|----------------------------------------------------------------------------------------------------------------|----------------------------------------------------------------------------------------------------------------------------------------------------------------------------------------------------------------------------------------------------------------------------------------------------------------------------------------------------|---------------------------------------------------|--------------------------------------------------------------------------|---------------|------------------------------------------------------------------------------------|-------------|-----------------------------------------------------------------------------------------------------------------------|----------------------------------------------|---------------------------------------------------------------------------------------------------------------------------------------------------------------------------------------------------------------------------------------------------------------------------------|-------------------------------|-------------------------------------------------------------|----------------------------------------------------------------------------------------------|
|                                                                                                                |                                                                                                                                                                                                                                                                                                                                                    |                                                   |                                                                          |               |                                                                                    |             |                                                                                                                       |                                              |                                                                                                                                                                                                                                                                                 |                               |                                                             |                                                                                              |

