## 6. Study design

A two-arm superiority parallel randomised controlled trial with an internal pilot study (see below), with measures taken at baseline (T1), scheduled within one month before randomisation and then at three months (T2 primary outcome, primary timepoint), six months (T3), nine months (T4) and 12 months (T5) post-randomisation.

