## **17. Data collection**

All OPTIMA trial data will be collected remotely: online, by phone and via video/audio chat. For each participant, assessments will take place over the period of 12 months and will be conducted at five timepoints as described above [baseline (T1), T2, T3, T4, T5]. The assessment window will cover a period of six weeks and will begin two weeks before the scheduled assessment and will close four weeks after the scheduled assessment. As a thank you for taking part, parents will receive shopping vouchers: £10 at baseline, £25 voucher at T2 and £10 voucher after completing T3, T4 and T5 assessments. Children will receive a £5 book voucher and a certificate for each completed task. The vouchers will be emailed to participants.

Four categories of data will be collected in the study: (1) participants' reports on the outcome measures and information about adverse events; (2) a speech sample audio-recorded during a remote parent-child drawing task (ESO); (3) the STEPS app usage data (for the intervention group only) and (3) video and audio recordings of qualitative interviews.

- (1) Outcome data and information about adverse events will be collected online using [Red Pill](#) – a secure electronic data capture and management system provided by Sealed Envelope or over the phone by a trained researcher.

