**In non-CTIMPs, a serious adverse event (SAE) is defined as an untoward occurrence that:**

- (a) results in death;
- (b) is life-threatening;
- (c) requires hospitalisation or prolongation of existing hospitalisation;
- (d) results in persistent or significant disability or incapacity;
- (e) consists of a congenital anomaly or birth defect; or
- (f) is otherwise considered medically significant by the investigator.

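### The Adverse Events Form has no code for the sixth criterion of the protocol's own SAE definition; the parent adverse event questionnaire also has one wrong skip and a fixed recall that can leave time not asked about

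*Protocol*

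**What the plan says.** **SAE definition.** Section 21.2.1 lists six alternatives: death, threat to life, hospitalisation, disability, congenital anomaly and, as (f), an event that "is otherwise considered medically significant by the investigator".

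**Adverse Events Form.** Field 10 in Appendix 4 asks whether the event is serious. It offers code 0 for No and codes 1 to 5, the last being "5. Consists of a congenital anomaly or birth defect". There is no sixth code and no 'other' option.

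**MAPED content and timing.** Under section 10.3.9, parents are asked at T1 to T5 to "report retrospectively any physical and/or mental health difficulties they or their child have experienced in the last three months". Section 6 places the later follow-ups at "six months (T3), nine months (T4) and 12 months (T5) post-randomisation", after T2 at three months. Under section 17 the assessment window "will begin two weeks before the scheduled assessment and will close four weeks after the scheduled assessment". Section 25.4 keeps a family in the trial if one timepoint is missed.

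**MAPED routing.** In Appendix 3, a No at question 5 (the child's relationship or daily-activity difficulties) is routed to Q4. A No at question 4 is routed to Q5. Question 6 asks about the parent's own difficulties, question 7 about concerns over taking part, and question 8 about good effects.

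**How reports are handled.** Section 21.1 has MAPED responses reviewed and adverse events entered on the form, together with any difficulty a parent discloses spontaneously. Section 21.2.2 has the chief investigator and a clinical expert assess each case for seriousness, expectedness and relatedness.

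**The concern.** The form is where the trial's judgement of seriousness is stored. If that judgement is reached under (f), the form cannot hold it. The entry will be either not serious or serious for a reason that does not apply, and an SAE tabulation built from field 10 will be too low or wrongly described. Seriousness matters under the protocol's own rules. It governs follow-up until resolution (section 21.1), immediate reporting to the chief investigator and sponsor (section 21.2.2), and whether an event listed as expected leaves the publication-only route (section 21.3).

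The two MAPED faults concern what reaches the form at all. A question that is skipped, or a period that is not asked about, cannot be repaired later from the recorded data.

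**Working it through.** **1. SAE criteria against field 10 codes**

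| Section 21.2.1 | Field 10 code |
|---|---|
| (a) death | 1 |
| (b) life-threatening | 2 |
| (c) hospitalisation or its prolongation | 3 |
| (d) persistent or significant disability | 4 |
| (e) congenital anomaly or birth defect | 5 |
| (f) otherwise medically significant | none |

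Six criteria are defined and five can be coded.

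**2. MAPED routing**

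As printed, Q4 No leads to Q5 and Q5 No leads to Q4. If Q4 is also No, the two questions loop. If Q4 is Yes, the parent comes back to Q5. No answer pattern with No at Q5 reaches Q6, Q7 or Q8. Every other printed skip moves forward. The items with a hospitalisation question (Q1 to Q4) are not affected.

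**3. Recall against the assessment window**

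The window figure reproduces: 2 weeks before + 4 weeks after = 6 weeks. I take three months as 13 weeks (91 days).

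Time not asked about = interval between two completed forms − 13 weeks of recall.

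| Situation | Interval (weeks) | Not asked about (weeks) |
|---|---|---|
| Both forms on schedule | 13 | 0 |
| First early, second on time | 13 + 2 = 15 | 2 |
| First on time, second late | 13 + 4 = 17 | 4 |
| First early, second late | 13 + 2 + 4 = 19 | 6 |
| One visit missed, others on schedule | 26 | 13 |
| One visit missed, first early, next late | 26 + 2 + 4 = 32 | 19 |

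Early and late here mean the extreme ends of the window.

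For T2 completed at window close, 17 weeks after randomisation, a 13-week recall starts at week 17 − 13 = 4. The first 4 weeks (28 days) after randomisation are then not asked about. That is 28/91 = 31% of the three-month access period.

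**4. Pre-randomisation events**

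T1 is completed before randomisation, so its recall lies wholly before the trial intervention. Section 21.2.1 defines an adverse event as occurring in someone to whom a therapy has been administered, which T1 events do not meet. Section 21.1 nevertheless sends MAPED responses at each timepoint to the same form. The start date in field 5 allows the two to be told apart.

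**The case against.** The best defence is that the form is not the safety pathway. Under section 21.2.2 the research team reviews all completed questionnaires, staff inform the chief investigator within 24 hours of an event meeting the SUSAR (suspected unexpected serious adverse reaction) definition, and seriousness is judged by the chief investigator with a clinical expert. Field 11 records SUSAR status separately and field 1 is free text. A reader might infer that SUSAR review hangs on the field 10 code. The protocol does not say so. Self-harm and child-protection concerns, the examples that come first to mind, are listed as expected in section 21.3 and so cannot be SUSARs. This part of the defence stands. What remains is a recording mismatch.

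A reader might also infer that adverse event counts by arm will mix duplicates with baseline events. That is not supported either. Questions 1 to 6 ask for start and end dates, and the form carries start date, outcome and end date in fields 5 to 7, so such entries can be separated.

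On recall, the gap is zero when forms are on schedule, and 6 weeks needs one form on the first day of its window and the next on the last. A problem still ongoing would be reported on the next form, spontaneous disclosures are recorded (section 21.1), and non-responders are telephoned until the window closes (section 17). This reduces the gap but does not close it: an event that began and resolved in the unasked period, and that the parent did not mention, is missed.

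The skip at question 5 is probably a typing slip. The database is configured specifically for the trial (section 18.1), and its live routing is not shown. The printed appendix is still wrong and needs checking against the live form.

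**Conclusion.** The point holds as an internal contradiction plus two lesser faults in an instrument.

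- **Firm:** one of six SAE criteria cannot be recorded in field 10. Section 21.2.1 and Appendix 4 must be reconciled. How many events this touches cannot be derived from the protocol. It is however many are judged serious under (f) alone.
- **Firm as printed, uncertain in practice:** a No at MAPED question 5 bypasses questions 6 to 8, including the question on concerns about taking part.
- **Conditional:** the recall can leave up to 6 weeks between adjacent follow-ups not asked about, the first 4 weeks after randomisation if T2 is at window close, and about 3 months after one missed visit (up to 19 weeks if the neighbouring forms also sit at the ends of their windows). These are upper limits that depend on completion dates, and they apply only to events that had resolved and were not disclosed.

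The primary efficacy analysis is not affected. The protocol gives no ground for saying that SUSARs will be missed or that comparisons of adverse events between arms are invalid.

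**What to change.** 1. **Field 10.** Add a sixth code worded as criterion (f), so that Appendix 4 and section 21.2.1 agree. Check events already entered as not serious against (f).
2. **MAPED question 5.** Route No to question 6 in Appendix 3 and check the live electronic form. If the live form follows the printed skip, note that questions 6 to 8 are missing by routing on the forms already completed.
3. **MAPED recall.** At T2, ask about the time since randomisation on [date]. At T3 to T5, ask about the time since the parent last completed the questionnaire on [date]. If T2 was missed, use the randomisation date on the first follow-up form completed. Have Red Pill fill in the dates.
4. **Pre-randomisation events.** State that events with a start date before randomisation, including those reported at T1, are history and are not counted as trial adverse events.

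**Cost.** Items 1 and 2 are small form edits and item 4 is a sentence. Item 3 has a real trade-off: a parent who completes T2 at week 11, misses T3 and completes T4 at week 43 would recall 43 − 11 = 32 weeks instead of 13. Recall over that length is less reliable, but the fixed wording does not ask about 19 of those weeks at all. For parents who complete on schedule the recall length is unchanged.
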